### Sample size

Given the growth patterns of preschool-age children, weight maintenance has been recommended as the goal as this will lead to a reduction in adiposity with expected linear growth [27]. For the power calculations, we used a mean BMI z-score of 2.5 with a standard deviation of 0.7 for the baseline measurements, based on a previous trial in a similar popuation [19]. A BMI z-score of 2.5 is equivalent to a mean of 120% of the 95th percentile BMI for age and gender. Weight maintenance at this age leads to roughly a 0.5-unit reduction in BMI z-score over 4–6 months among children with obesity, a clinically meaningful reduction. We assumed a standard deviation of 1.0 for the 0.5-unit change in BMI z-score over 6 months. With these assumptions and to achieve 80% power at an alpha of 0.05, we would need 64 children per group to complete the 6-month assessment to detect this clinically meaningful difference of 0.5-unit reduction in BMI z-score between the two active intervention groups. We did not include a repeated measures correlation coefficient in our sample size calculation. We estimated a roughly 25% dropout rate by 6 months given the mobility of the targeted population, and so we aimed to recruit and enroll 80 dyads per group (240 parent–child dyads in total).

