### Data analysis

Given the relatively high potential for missing data because of attrition in the population enrolled over time, we plan a procedure of multivariate imputation by chained equations. Variables to be included in the multiple imputation model include BMI z-score of the child, child age, gender, family income, and language. This procedure operates under the assumption that the missing data are missing at random. A pattern mixture model will be applied to examine the informativeness of missing outcome data using time at 6 and 12 months to examine interactions with missing data patterns. The results of the pattern mixture model will be incorporated as a fixed effect in the linear mixed model (described below).

Using an intention-to-treat analysis, we will assess the primary outcome of mean change in adjusted BMI z-score at the end of the active period of intervention and use an alpha of 0.05. We will use linear mixed models to analyze the primary outcome of change in adjusted BMI z-score looking at the main effect of randomization group, time, and their interaction by using Wald tests for statistical significance and Akaike information criterion to assess model fit. A cohort variable, defined as the period of enrollment given multiple enrollment periods over the course of the study, will be included as a fixed effect. Baseline BMI z-score will be examined as a covariate. All models will be examined for the normality, homoscedasticity, and linearity of the residuals to ensure that the assumptions of the models are met.

Secondary outcomes will be analyzed by using similar methods, comparing by randomization group. We will adjust all secondary outcomes for multiple comparisons by using the Holm–Bonferroni method. We will track participation with a potential secondary analysis carried out stratifying by levels of participation. All quantitative analyses will be completed by using SPSS software version 24 (IBM Corporation, Armonk, NY, USA).

We will employ three regression equations to complete planned mediation analyses of intervention effects by the secondary outcomes. These include the main intervention effect on the primary outcome, change in adjusted BMI z-score, the main intervention effect on the mediating variables (secondary outcomes), and the combination of the intervention effect and mediating variables on the primary outcome. We will use a product-of-coefficients approach to examine the potential mediators [45].

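### The stated imputation list leaves out the mediators and the randomization group, so BMI values imputed from it would understate indirect effects if they are used in the planned mediation analysis

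*Protocol article*

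**What the plan says.** The Data analysis section of the protocol article opens with missing data: "we plan a procedure of multivariate imputation by chained equations". It gives the contents of the model: "Variables to be included in the multiple imputation model include BMI z-score of the child, child age, gender, family income, and language". It adds: "This procedure operates under the assumption that the missing data are missing at random". Neither the secondary outcomes nor the randomization group is on the list.

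The same section then sets out the mediation analysis: "We will employ three regression equations to complete planned mediation analyses of intervention effects by the secondary outcomes". The third of these equations is described as "the combination of the intervention effect and mediating variables on the primary outcome". The estimator is also fixed: "We will use a product-of-coefficients approach to examine the potential mediators". On the secondary outcomes themselves, the section says: "Secondary outcomes will be analyzed by using similar methods, comparing by randomization group".

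Two other places matter. Sample size sets the expected loss: "We estimated a roughly 25% dropout rate by 6 months given the mobility of the targeted population", with 80 dyads enrolled per group. Secondary outcomes places most mediators at baseline, 6 and 12 months in all three arms. The home food environment is the exception: it is measured at baseline and 4 months, in the two mentor arms only.

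**The concern.** An imputation model should contain every variable that the later analysis relates to the imputed one. Call the three equations E1 (arm on change in adjusted BMI z-score), E2 (arm on mediator, slope a) and E3 (arm and mediator on change in adjusted BMI z-score, mediator slope b). The indirect effect is a × b. If a child's 6-month BMI is drawn without reference to the mediator, then in that child BMI and mediator are related only through whatever the imputation model does contain. Mixing such children with fully observed ones pulls b toward zero.

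The intervention was built by mapping behaviors to their determinants, and mediation is the planned test of that chain. A diluted b makes a real mediator look weak. Where arm is in the imputation model, the lost part of the indirect effect is credited to the direct effect. Of the mediators, the home food environment is the most exposed. It is the first of the four core behaviors and the first month's topic in the experimental curriculum. Because it is collected at 4 months, it can be present when the 6-month BMI is missing.

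**Working it through.** **The plan's own figure.** For a difference of 0.5, SD 1.0, alpha 0.05 (two-sided assumed) and 80% power, n = 2(1.96 + 0.84)² × 1.0² / 0.5² gives 63 per group by the normal formula and 63.77, so 64, by the t-test. The stated 64 is reproduced. At the stated 25% loss, 80 × 0.75 = 60 complete. Retaining 64 of 80 corresponds to 20% loss. Both rates are checked below. The article gives no figure for the indirect effect.

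**Expected size.** Let d be the share of analysed children whose BMI is imputed without the mediator. With baseline BMI in E3, b becomes about (1 − d)b.
- Mediator observed, or imputed separately with arm in the model: a is intact, so the ratio of estimated to true indirect effect is 1 − d = 0.75 at d = 0.25.
- Mediator also imputed separately and arm left out: a shrinks as well, so the ratio is (1 − d)² = 0.75² = 0.56.
- Without baseline BMI in E3, part of the link survives through baseline BMI, so the loss is smaller.

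**Simulation.** The effects are assumptions and are not in the article: a = 0.5, b = −0.4 (indirect effect −0.200 with baseline adjusted), direct effect −0.2, coefficient of baseline BMI 0.3 on the mediator and −0.3 on the outcome. There were 1,000,000 records in two equal arms, loss completely at random, and one regression imputation with random error from baseline BMI, with or without arm. The table gives the ratio of estimated to true indirect effect. In each cell the first value adjusts E2 and E3 for baseline BMI and the second does not.

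| Handling | 20% missing | 25% missing |
|---|---|---|
| Mediator not imputed; dropouts leave E2 and E3 | 1.00 / 1.00 | 1.00 / 1.00 |
| Mediator observed, BMI imputed, arm in | 0.80 / 0.85 | 0.75 / 0.81 |
| Mediator observed, BMI imputed, arm out | 0.80 / 0.85 | 0.75 / 0.81 |
| Both imputed separately, arm in | 0.80 / 0.85 | 0.75 / 0.82 |
| Both imputed separately, arm out | 0.64 / 0.68 | 0.57 / 0.61 |
| Joint imputation, arm in | 0.99 / 1.00 | 0.99 / 1.00 |

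At 25% missing, the loss with arm in is 1 − 0.75 = 25% with baseline adjusted and 18-19% without. With both imputed separately and arm out, it is 1 − 0.57 = 43% and 1 − 0.61 = 39%.

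**At trial size.** 1,500 simulated trials with 80 per arm, 5 imputations, arm in both separate models, and assumed baseline coefficients of 0.6 (outcome) and 0.4 (mediator) gave indirect effects of −0.160, −0.149 and −0.129 at 20%, 25% and 35% missing, against a true −0.200. Joint imputation gave −0.200 to −0.201.

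**Home food environment.** The observed-mediator rows assume that every child with missing 6-month BMI has the 4-month assessment. If only half did (an illustration), 12.5% of children would enter E3 with imputed BMI beside 75% observed, so d = 12.5 / 87.5 = 14%.

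**The case against.** The strongest reply is that the article never describes the procedure that does the damage. It does not say that the mediation regressions use imputed data, that mediators are imputed, or that they are imputed apart from BMI. The sentence on analyzing secondary outcomes in a similar way comes after the mixed-model text and most naturally refers to that model. Read literally, a variable outside the imputation model is not imputed. A child who misses the 6-month visit lacks both BMI and most mediators, and so leaves E2 and E3. The slope is then not diluted under completely random loss. Because the product of coefficients uses only E2 and E3, it does not need the total effect from E1. The list is also introduced by a verb that need not be exhaustive, in an article that condenses a fuller protocol.

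Much of this stands. A reader might infer that the mediator-outcome link is erased in a quarter of children and that every indirect effect will come out a quarter too small. The article does not support that. The dilution needs imputed BMI in E3, one reading gives no dilution at all, and without baseline adjustment part of the link survives. A flat quarter also reads the list as closed for mediators but open for arm.

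The mismatch itself remains. The article prints a concrete list beside an analysis that the list does not fit, and nothing in the text points to mediators being added. On the literal reading, the imputation brought in to deal with attrition does not serve the mediation analysis. For the home food environment, joint missingness at the 6-month visit is no protection.

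**Conclusion.** The point holds in conditional form. The stated imputation model omits the mediators and the randomization group, and BMI values imputed from it should not enter the mediation regressions. If they do, beside observed or separately imputed mediators, the indirect effect is understated by about 18-25% at 25% missing with arm in the model. The understatement is about 40% if arm is also omitted and mediators are imputed separately. If mediators are left unimputed, the understatement is 0% under completely random loss. The costs are then about 60 completers per arm in E2 and E3, a complete-case assumption, and an E1 that rests on a different sample, so total, direct and indirect effects need not add up. The full range is therefore 0% to about 43%, depending on a choice that the article does not fix.

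The percentages rest on assumed effects, loss completely at random, and baseline BMI being in the imputation model. The rule that b shrinks by the imputed fraction, with baseline adjusted, does not depend on the particular a and b chosen. Omitting the mediators does not affect the primary comparison between the two mentor arms; the problem is confined to the mediation analysis.

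**What to change.** State that the mediation analyses use imputed data, and specify the model for them:
- Impute adjusted BMI z-score and each mediator (scale totals, not items) jointly in one chained-equations model, at the visits where each is collected, with randomization group and the variables already listed.
- If that model is too large for 240 children, run one joint model per mediator.
- Fit E1, E2 and E3 on the same imputed data sets, so that total, direct and indirect effects refer to the same children.
- For the home food environment, use its baseline and 4-month values and restrict the imputation and all three equations to the two mentor arms, since it is not collected in the control arm by design.

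No new data are needed. The cost is a few sentences of analysis text, a larger imputation model and more computing time. Using scale totals or one mediator at a time keeps the model manageable.

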##### Acculturation

The Brief Acculturation Scale for Hispanics (BASH) is administered to parents to assess their degree of acculturation [41]. The BASH has high internal consistency (Cronbach’s alpha = 0.94 overall). This measure assesses language use in different contexts. We added a question specific to dietary acculturation [42]. Parental country of birth and length of time in the US are also collected.

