A challenge in the recruitment lies in the population served, namely that the migrant and seasonal farmworkers who make up a large proportion of the population move locations. Although the intervention can be adapted to the seasonal schedules and the parent mentors provide a viable and flexible method of contact, the challenge of retention remains. Maintaining contact to evaluate the 12-month time point, 6 months after the intervention has ended, may be a challenge.

Once this study is completed, the results will have implications for Head Start programs seeking to address obesity. One of the limitations in applying this design more broadly is the fact that parent mentors are provided with financial incentives. It will not be clear how feasible this study would be without the parent mentor or parent mentee subject payments for their time. However, the goal of this trial is to test effectiveness with fidelity relatively controlled and so we consider the financial payments necessary, particularly given the length of evaluations for the parent participant.

Most of the documented interventions to reduce obesity in the context of a Head Start program have been program-wide implementation of health promotion curricula [48–51]. This study represents one of the few targeted interventional studies in that it specifically identifies children with obesity for recruitment and participation. One might argue that most if not all parents could benefit from a parent mentoring program to support these parenting skills. However, given the resources required to support the parent mentors and the finding that (overall) many children do experience some reduction in adiposity with usual Head Start participation [52], we think this stratification is appropriate.

In summary, this article describes one of the few clinical trials designed for a low-income, Latino population of preschool-age children with obesity [49, 51, 53]. This demographic has one of the highest risks for continuing to have adult obesity and diabetes [4]. Data informing the best treatment approaches for this population are urgently needed and these types of clinical trials can help provide that information.

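### The named imputation variables omit family mobility, the plan's stated reason for loss, and also participation and enrolment cohort, which the trial holds

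*Protocol article*

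**What the plan says.** In the protocol article, the Data analysis section chooses the method: "we plan a procedure of multivariate imputation by chained equations". It names the inputs: "Variables to be included in the multiple imputation model include BMI z-score of the child, child age, gender, family income, and language". It then states the assumption: "This procedure operates under the assumption that the missing data are missing at random".

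A safeguard follows at once: "A pattern mixture model will be applied to examine the informativeness of missing outcome data using time at 6 and 12 months". The results of that model are to enter the linear mixed model as a fixed effect. The same section puts an enrolment-period cohort variable into the analysis model as a fixed effect. On exposure it says: "We will track participation with a potential secondary analysis", stratified by level of participation.

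The cause of loss is given in two places. Under Sample size: "We estimated a roughly 25% dropout rate by 6 months given the mobility of the targeted population". In the Discussion, retention is called a challenge because "the migrant and seasonal farmworkers who make up a large proportion of the population move locations". Under Acculturation the article adds: "Parental country of birth and length of time in the US are also collected".

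**The concern.** Missing at random is not a property of the data alone. It holds, or fails, given the variables in the imputation model. Here the article names the force that it expects to remove about a quarter of the children, and then conditions on five variables of which none measures it. Two items that could carry part of that information are at hand but not on the list: participation and enrolment cohort. Cohort is a plausible proxy for seasonal movement.

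The primary comparison is between the two mentor arms at 6 months, by intention to treat. The target therefore includes the actual outcomes of families who left. Those outcomes will be predicted from observed families who are alike on the listed variables. If the observed families are on average more settled, or received more of the programme, and if either feature changes how much the curriculum matters, the imputed values will carry too much of the effect.

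**Working it through.** **The plan's own figure.** Inputs from Sample size: difference 0.5, SD 1.0, alpha 0.05, power 80%. A two-sided two-sample t-test needs 63.8, so 64 per group, as stated (63 by the normal approximation). I use 0.5 as the reference effect. Enrolling 80 per group with 25% loss leaves 80 × 0.75 = 60 observed and 20 imputed per arm.

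**Candidate variables against the list.**

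| Variable | Held by the trial? | On the imputation list? |
|---|---|---|
| Migrant or seasonal status | Not stated | No |
| Participation | Yes, tracked | No |
| Enrolment cohort | Yes, in the analysis model | No |
| Time in the US, country of birth | Yes | No |

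**Assumptions.** The article gives no share of mobile families, no loss by mobility and no effect in leavers. All inputs below are therefore assumed. Arm is taken to be in the imputation model, although the list does not name it.

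**Case 1: mobility changes the effect.** Let half of families be mobile, with effect 0.5 in settled families and e in mobile ones. The mobile share among observed families is s = 0.5(1 − loss in mobile) / [0.5(1 − loss in mobile) + 0.5(1 − loss in settled)]. The truth is 0.5e + 0.5 × 0.5. Imputation without mobility gives s·e + (1 − s) × 0.5. The overstatement is (0.5 − s)(0.5 − e).

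| Loss, mobile/settled | s | e | Truth | Imputed | Overstatement |
|---|---|---|---|---|---|
| 40%/10% | 0.30/0.75 = 0.40 | 0 | 0.25 | 0.30 | 0.05 (20%) |
| 40%/10% | 0.40 | 0.2 | 0.35 | 0.38 | 0.03 (9%) |
| 40%/10% | 0.40 | 0.3 | 0.40 | 0.42 | 0.02 (5%) |
| 45%/5% | 0.275/0.75 = 0.367 | 0 | 0.25 | 0.317 | 0.067 (27%) |

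Both loss pairs average 25%.

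**Case 2: leavers keep a fraction f of the effect.** Truth = 0.75 × 0.5 + 0.25 × 0.5 × f = 0.375 + 0.125f, against an imputed 0.5.

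| f | Truth | Overstatement |
|---|---|---|
| 0.25 | 0.406 | 0.094 (23%) |
| 0.5 | 0.438 | 0.063 (14%) |
| 0.75 | 0.469 | 0.031 (7%) |
| 1 | 0.5 | 0 |

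The extreme f = 0 gives 0.125.

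**Case 3: leavers differ by the same amount δ in both arms.** The bias in the contrast is δ × (difference in loss between arms). With equal loss it is 0. With 20% against 30% loss and δ from 0.1 to 0.5, it is 0.01 to 0.05, in a direction set by which arm loses more.

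**Simulation** (4,000 replicates, 80 per arm, 35% movers with no effect, 55% loss in movers and about 9% in others, so 25% overall). Differences are given as sizes of reduction.
- True difference: 0.33 (by hand, 0.65 × 0.5 = 0.325).
- Imputing from baseline BMI z-score and arm: 0.40. By hand, movers are 0.35 × 0.45/0.75 = 0.21 of observed families, and 0.79 × 0.5 = 0.395.
- Adding mobility and its interaction with arm: 0.33.
- Leaving arm out as well: 0.30, below the truth. The direction stated here thus depends on arm being in the imputation model.

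**Scale.** With 60 observed per arm, the standard error of the contrast is about 1.0 × √(2/60) = 0.18. An overstatement of 0.09 is about half of that.

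**The pattern mixture model.** A pattern term fitted to values already imputed under missing at random brings in no information on leavers' unseen 6-month outcomes, and no departure from that assumption is stated. Children missed at 6 months but seen at 12 may help a little. Families who leave for good do not.

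**The case against.** The strongest case against has five parts.

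- **The plan does examine missing at random.** The pattern mixture model is meant for leavers who differ from stayers. This stands as far as it goes: a reader who infers that the assumption goes unexamined would be wrong. As described, though, the model does not repair the imputed values.
- **The list may not be exhaustive.** It is introduced with the word include, and fuller detail may sit elsewhere. That is possible. Still, the article chose to name variables, and the names leave out the driver that it states.
- **Leaving is not the same as stopping treatment.** Mentors coach weekly by phone, text or in person, and the Discussion calls them a flexible route of contact. A family that moves may miss only the visit. This stands, and is why Case 2 is an assumption. Recorded participation is what would tell the two situations apart.
- **The primary arms share format and frequency.** Bias there needs mobility or exposure to alter the curriculum difference, or loss to be unequal. This also stands.
- **Some candidate variables are weak.** No section links time in the US or country of birth to moving during follow-up. Centre could cost too many parameters with about 60 observed children per arm. Migrant or seasonal status may not be held. These points limit the fix to what is listed below.

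Two stronger readings are tempting. One is that leavers are imputed as if they were settled families who completed the programme. The documents do not support it: the model draws on every family with an observed outcome, including mobile and low-participation ones (40% mobile in the first scenario of Case 1). The other is that the plan names low programme exposure as a cause of loss. It names only mobility; participation is merely tracked.

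**Conclusion.** The point holds in a limited form. The named list omits any measure of the one cause of loss that the article states, and omits participation and enrolment cohort, which are available. Missing at random is therefore less plausible than it could be at almost no cost.

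With arm in the imputation model and leavers who keep less of the curriculum effect, the overstatement is roughly 0.02 to 0.09 units on a design effect of 0.5. It is zero if leavers keep the effect, or if they differ equally in both arms and loss is equal. All of these sizes rest on assumed inputs. They show what could happen and do not show that the primary result will be biased. The change is worth making before analysis, but the omission does not invalidate the design.

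**What to change.** Amend the sentence that names the imputation variables:

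- Add participation up to last contact, in the two mentor arms. It is defined in both arms of the primary comparison. Because it is measured after randomisation, use it for imputation only and not as a covariate in the primary analysis model.
- Add enrolment cohort, so that the imputation model contains what the analysis model contains.
- Add migrant or seasonal status if the Head Start record holds it.
- Impute by arm, or with arm interactions, so that these variables can act differently by arm. Imputing by arm also deals with participation in mentoring being undefined under usual care.
- State that missing at random is assumed given this set.

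Keep the set small. Time in the US and country of birth are optional weak proxies, and centre should enter only if the number of centres allows.

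The cost is a change of wording, a check of what the intake record holds, and a few more parameters in the imputation equations. No new data collection is needed.

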### Outcome measures

#### Primary outcome

The primary outcome is change in adjusted BMI z-score at the end of the active intervention period, 6 months post-enrollment. Adjusted BMI z-scores account for child age and gender and allow the evaluation of changes in BMI z-scores within the upper range of z-scores expected during this trial [28]. Adjusted BMI z-score is assessed in all three arms. The primary comparison is between the two active intervention groups at 6 months. The 12-month time point serves as an evaluation of maintenance of any changes post-intervention (Fig. 3).

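### The primary mixed model carries a missing-data-pattern term with no stated averaging over patterns, so the 6-month treatment contrast may be conditioned on later dropout

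*Protocol article*

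**What the plan says.** All the relevant text is in the Protocol article.

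- Data analysis, first paragraph, plans chained-equation imputation and states its assumption: "This procedure operates under the assumption that the missing data are missing at random".
- The same paragraph adds a second method: "A pattern mixture model will be applied to examine the informativeness of missing outcome data using time at 6 and 12 months". It then fixes what happens to the output: "The results of the pattern mixture model will be incorporated as a fixed effect in the linear mixed model (described below".
- The next paragraph describes that mixed model. It is the primary analysis ("Using an intention-to-treat analysis, we will assess the primary outcome of mean change in adjusted BMI z-score"), and inference comes from "looking at the main effect of randomization group, time, and their interaction by using Wald tests for statistical significance".
- Primary outcome sets the target: "The primary comparison is between the two active intervention groups at 6 months".

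The pattern step is not called a sensitivity analysis. The article does not say exactly what the results of the pattern model are, whether pattern interacts with group, or whether effects are averaged over patterns before testing.

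**The concern.** A child's missing-data pattern is known only after randomisation, and both arm and response can affect it. Once it is a fixed effect, the group and group-by-time coefficients compare arms among children with the same pattern. That is not the comparison of all randomised children that an intention-to-treat analysis claims to make. If pattern also interacts with group, the printed group coefficient refers to the reference pattern alone.

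The timing sharpens the problem. The primary contrast is at 6 months, but patterns are built "using time at 6 and 12 months to examine interactions with missing data patterns". A family whose child did poorly at 6 months may be less likely to return at 12. Holding 12-month dropout fixed then adjusts the primary outcome for one of its own consequences, even though the 6-month value was observed and needed no correction.

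At stake are the size of the primary effect and, under no effect, a false difference between the two active arms.

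**Working it through.** **Inputs from the Protocol article, Sample size.** Difference 0.5, SD of change 1.0, about 25% dropout by 6 months, 80 dyads per group. The plan's figure reproduces: n = 2 × (1.960 + 0.842)² × (1.0/0.5)² = 62.8, so 63 by the normal formula; the t-test gives 63.8, so 64 per group, as stated. This confirms the scale used below but does not bear on the pattern term.

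**Assumed, because the documents give no figures.** Dropout between 6 and 12 months, and its odds ratio (OR) per SD of 6-month outcome.

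**1. Algebra.** Let Y be the 6-month change, observed; G the arm; D = 1 if the child is lost by 12 months; Δ the true difference; p₁ and p₀ the proportions lost. In a large sample, the arm coefficient from regressing Y on G and D is

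b = Δ − γ × (p₁ − p₀),

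where γ is the mean within-arm difference in Y between children later lost and children retained, weighted by p(1 − p). Without D, b = Δ. The bias is zero if γ = 0 (dropout unrelated to outcome) or p₁ = p₀.

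**2. No true effect, unequal dropout.** Y is standard normal and logit P(D = 1) = a + ln(OR) × Y, with a = −0.6 in one arm and −1.6 in the other.

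- OR 2: p = 0.368 and 0.188, γ = 0.635; b = 0 − 0.635 × 0.179 = −0.114.
- OR 1.5: p = 0.359 and 0.175, γ = 0.393; b = 0 − 0.393 × 0.184 = −0.072.

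Swapping the arms reverses the sign.

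**3. True difference −0.50, no direct arm effect on dropout.** The same intercept a applies in both arms. Dropout still differs by arm, because the treatment effect shifts Y.

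| a | OR per SD | p₀ | p₁ | γ | b |
|---|---|---|---|---|---|
| −1.3 | 1.5 | 0.222 | 0.190 | 0.395 | −0.49 |
| −1.3 | 2 | 0.235 | 0.182 | 0.643 | −0.47 |
| −1.3 | 3 | 0.258 | 0.180 | 0.921 | −0.43 |
| −0.6 | 1.5 | 0.359 | 0.316 | 0.391 | −0.48 |
| −0.6 | 2 | 0.368 | 0.298 | 0.631 | −0.46 |
| −0.6 | 3 | 0.382 | 0.283 | 0.895 | −0.41 |

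Example, fifth row: −0.50 − 0.631 × (0.298 − 0.368) = −0.456.

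**4. Check in a two-visit repeated-measures model.** Simulation of 400,000 children per scenario, true difference −0.50, assumed visit correlation 0.5, 25% missing at 6 months.

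- No pattern term: −0.50 to −0.505 in all six scenarios.
- Pattern main effect: −0.50 when dropout is random or differs by arm only; −0.49, −0.47 and −0.43 at OR 1.5, 2 and 3; −0.54 at OR 2 with an added arm effect on dropout. That last scenario gives −0.08 when the truth is 0.
- Pattern and pattern-by-group, averaged over each arm's pattern mix: −0.50 to −0.505 again.

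**5. What the term does not cause.** Apply step 2's mechanism to dropout at 6 months, so that Y itself is missing. A completers-only comparison with no pattern term is then off by about −0.11 (OR 2) or −0.07 (OR 1.5). Missing-at-random imputation within arm gives the same error. Adding the pattern term to the imputed data changes nothing.

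**6. Scale.** With 80 × 0.75 = 60 children per arm, the standard error is √(2 × 1.0²/60) = 0.18. The shifts of 0.02 to 0.09 in step 3 rows four to six are about 0.1 to 0.5 standard errors; the 0.07 to 0.11 in step 2 is about 0.4 to 0.6.

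**The case against.** Pattern terms as fixed effects are the ordinary first stage of a pattern mixture analysis. Averaging the pattern-specific effects restores the marginal effect, as step 4 shows. The article is silent on averaging, and a condensed article may leave that to a fuller document. This stands against the stronger inference that the plan necessarily destroys its intention-to-treat estimate; the text does not go that far. It does not remove the point. The article specifies Wald tests of model coefficients, and averaging first is a different procedure from the one described.

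The wording is also loose: the results of the pattern model need not be a pattern indicator. That is fair, but on any other reading the primary model is not determined by its own description, so the sentence still needs changing.

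The sizes rest on assumed odds ratios. The Sample size section and the Discussion attribute attrition to family mobility, which may have little to do with response. This stands, and it is why the bias is described as conditional.

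A reader might infer that imputing under missing at random while also fitting a pattern mixture model is a contradiction. It is not: examining departures from a declared assumption is good practice. The weakness is that the two are not given separate roles.

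A reader might also infer that deleting the term cures dropout bias. Step 5 shows that it does not when dropout at 6 months itself depends on the outcome.

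**Conclusion.** The point holds as a correction that should be made, with modest consequences. As most naturally read, the article conditions the primary 6-month contrast on post-randomisation dropout, including dropout that occurs after the outcome was measured, and it states no averaging back to the randomised groups.

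Where 6-month values are observed and 12-month dropout depends on them (OR 1.5 to 3 per SD, no direct arm effect on dropout), a true −0.50 is reported as about −0.48 to −0.41 with some 28% to 38% lost later, and slightly closer to the truth with fewer lost. With a direct arm effect on dropout the error can instead run the other way (−0.54 in one scenario). Under no effect, the false difference is about 0.07 to 0.11 SD at OR 1.5 to 2 with roughly twice the dropout in one arm; its sign depends on which arm loses more children. There is no bias if dropout is unrelated to outcome or, under no effect, unrelated to arm. None of the dropout mechanisms is documented.

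**What to change.** In Data analysis, remove the sentence that puts the pattern mixture results into the primary mixed model, and name the missing-at-random analysis (imputation and mixed model) as primary.

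Keep the pattern mixture model as a sensitivity analysis in one of two forms:

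- pattern-by-group effects averaged over the pattern proportions observed in each arm; or
- delta-adjusted imputation by arm over a stated range of shifts, which also addresses children with no 6-month value.

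Report whether the 6-month conclusion holds across these analyses.

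The cost is a change of analysis wording and a little extra analysis. No visits, data or sample size change.
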